#### Health services utilization

Standard methods to measure health services use using provincial claims data will be used. All physician visits, emergency department visits, hospitalizations and medication claims during the 12 months following index prescription will be identified using the RAMQ data through MOXXI.

#### Intervention costs

We will record the entire amount of time the study pharmacist spends supporting patients in the intervention group. This will allow us to calculate costs at the patient level as well as aggregated at the population level. We will also track implementation and support costs for the IVRS, including calling charges. These costs will be prorated across the study population.

#### Explanatory variables

To determine factors that influence outcomes, we will use data in the MOXXI system to derive baseline information on patients, including demographic information (age, gender, language of choice and location of residence), active and past medical diagnoses and medication use in the preceding year (number of new drug starts and adherence).

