### Setting

This research will occur during ambulatory care in the province of Québec, Canada. We will study prescriptions in patients receiving primary care from a selected group of physicians using the Medical Office of the 21st Century (MOXXI) electronic health record system. MOXXI was developed by the McGill University’s Clinical and Health Informatics Research Group. It is currently used by over 100 primary care physicians in Montréal and Québec City. The MOXXI system is linked to the provincial insurance company, Régie de l’assurance maladie du Québec (RAMQ), resulting in an electronic medical record that displays a drug profile of prescribed as well as dispensed drugs, emergency department visits and hospitalizations in the past 12 months, a list of active and past health problems, and an electronic prescribing tool. Data stored by MOXXI have been used by the McGill research team for medical research in the past
[3, 4].

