### Secondary objectives

Determine whether the ISTOP-ADE system, compared to routine care, will reduce the probability of a patient experiencing a severe ADE (defined as an ADE lasting at least 7 days or causing an emergency department visit).Determine whether the ISTOP-ADE system, compared to routine care, will reduce the proportion of patients experiencing ADEs, preventable ADEs and ameliorable ADEs.Determine whether the ISTOP-ADE system, compared to routine care, will reduce health services utilization (comprising physician visits, emergency department encounters and hospitalizations) at 12 months following an incident prescription.Measure the costs associated with the ISTOP-ADE system.

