### Data management and analysis

Data will be exported from the MOXXI system and analyzed using SAS software (Cary, NC, USA). All data analysis will be performed in secure physical locations using hardware that is password protected. Only study personnel will have access to the data. Simple descriptive statistics to describe the patient population, call statistics and outcome measures will be used. Continuous variables will be described using median and inter-quartile ranges, while categorical variables will be described using frequency distributions. The statistical significance of any associations between group assignment and measures will be assessed using the Wilcoxon rank sum test and or the chi-square test, respectively, for continuous and categorical variables. Since the primary outcome is binary, tests to compare outcomes between the intervention and control groups will be simple chi-square statistics. An alpha of 0.05 as a threshold to determine statistical significance using a two-tailed distribution will be applied.

As a sensitivity analysis, logistic regression modeling will be used to assess possible baseline factors that are associated with the outcome and differ between the intervention and control groups. Analogous analyses to assess significance for the individual components of the composite primary outcome and the binary secondary outcome variables will also be performed (ADE occurrence, preventable ADE occurrence and ameliorable ADE occurrence).

To compare health services utilization, since the outcomes are event data, which follow a Poisson distribution, incidence rates for the outcome will be calculated. Incidence rates will be calculated using PROC GENMOD to create a *t*-test. Multivariable Poisson regression will be used to compare the rates, while adjusting for baseline factors. The model will use the treatment group as an independent covariate. If over-dispersion is noted, a negative binomial model will be used.

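### The utilization analysis does not name the patient's own prior-year utilization as a covariate, although MOXXI already shows part of it: an avoidable loss of precision on a secondary outcome

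*Protocol article*

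**What the plan says.** The third secondary objective is to show that the intervention "will reduce health services utilization (comprising physician visits, emergency department encounters and hospitalizations) at 12 months following an incident prescription".

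Under Explanatory variables, the protocol states that "we will use data in the MOXXI system to derive baseline information on patients, including demographic information" (age, gender, language, residence), followed by "active and past medical diagnoses and medication use in the preceding year (number of new drug starts and adherence". Medication use is the only item there with a stated one-year look-back. Prior emergency visits, hospitalizations and physician visits are not mentioned.

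Under Setting, the record that MOXXI displays is said to contain "emergency department visits and hospitalizations in the past 12 months". Prior-year physician visits are not mentioned there.

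Under Data management and analysis, utilization is compared in two ways:
- "Incidence rates will be calculated using PROC GENMOD to create a *t*-test". No covariates are stated for this step.
- "Multivariable Poisson regression will be used to compare the rates, while adjusting for baseline factors". The factors are not listed. The fallback is: "If over-dispersion is noted, a negative binomial model will be used".

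**The concern.** Each utilization component has a direct baseline counterpart, the same patient's count in the year before the index prescription. For recurrent health-care use, that count is usually among the best available predictors of the later one, because some patients are persistently heavy users. The protocol itself foresees over-dispersion, which such differences between patients produce.

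A negative binomial model makes the standard error reflect that spread. It does not explain the spread. A prior-year count in the model can explain part of it, and so narrow the interval for the rate ratio and reduce the influence of a chance imbalance in heavy users. Enrolment is fixed at 1,100 per arm and was sized on persistence, so utilization gets whatever precision that number happens to give.

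As written, an analyst has no instruction to use this covariate, and nothing says which of the two comparisons is the main one.

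**Working it through.** **1. What the text specifies.**

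| Component | Prior-year value shown in MOXXI (Setting) | Named under Explanatory variables | Named in the utilization model |
|---|---|---|---|
| Emergency visits | yes | no | no (unlisted baseline factors) |
| Hospitalizations | yes | no | no (unlisted baseline factors) |
| Physician visits | not stated | no | no (unlisted baseline factors) |

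**2. Inputs.** From the protocol: 1,100 enrolled per arm, 10% loss to follow-up, two-sided α = 0.05. Evaluable patients: 2 × 1,100 × 0.90 = 1,980, or 990 per arm. The protocol gives no utilization rate, dispersion, effect size, year-to-year correlation or power, so it has no figure to reproduce. Everything below is over assumed ranges.

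**3. Gain against no adjustment.** With correlation r between the prior-year and follow-up measures, the variance of the treatment effect is multiplied by 1 − r². The interval width is multiplied by √(1 − r²), and the effective sample size becomes 1,980/(1 − r²). If unadjusted power is assumed to be 60%, adjusted power is Φ[(1.96 + 0.253)/√(1 − r²) − 1.96].

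| r | Variance reduction | Interval narrower by | 1,980 patients act like | Power, from 60% |
|---|---|---|---|---|
| 0.3 | 9% | 4.6% | 2,176 | 64% |
| 0.5 | 25% | 13.4% | 2,640 | 72% |
| 0.6 | 36% | 20.0% | 3,094 | 79% |

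**4. Gain beyond another baseline covariate.** The planned multivariable model already adjusts for something, so step 3 overstates what that model would gain. A simulation used 990 per arm, a true rate ratio of 0.85 and 150 runs per scenario. Counts were Poisson with log-normal patient effects correlated across the two years. One further baseline covariate x predicted use in both years. Negative binomial models with treatment + x were compared with treatment + x + log(prior count + 0.5). The variance reduction is 1 − (ratio of mean model standard errors)².

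| Mean per year | Correlation of the two counts | Ratio of standard errors | Variance reduction |
|---|---|---|---|
| 0.5 | 0.17 | 0.9957 | about 1% |
| 0.5 | 0.29 | 0.9772 | about 5% |
| 5 | 0.47 | 0.9565 | about 9% |
| 5 | 0.67 | 0.8418 | about 29% |

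In the rare-count scenarios, simulated power did not visibly change (58% and 58%; 57% and 56%). In the frequent-count scenarios it was already 97% or higher with x alone, so the benefit there is a narrower interval.

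**The case against.** The strongest reply is that the plan does adjust. The second utilization model is explicitly multivariable, its factors are unlisted, and nothing excludes prior use. The baseline list is open, since it is introduced as including certain items. Its stated purpose is to find factors that influence outcomes, and it is not presented as the covariate list of that model. A condensed article may also leave the exact covariate set to an analysis plan. This stands to the following extent: a reader might infer that the utilization comparison omits prior use altogether, and the text does not support that. What can be said is that prior use is not named.

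A reader might also infer a large and free gain in power. That is not supported either. The larger figures in step 3 are against no adjustment, whereas diagnoses, new drug starts and prior adherence may already carry part of the same variation. The gain and the available data also do not line up well. The prior-year data that MOXXI is said to display cover emergency visits and hospitalizations, which are plausibly the rarer counts with the smallest added gain. Physician visits, where the gain is plausibly larger, are not said to be held for the prior year.

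The negative binomial fallback already deals with the validity of the standard error, and randomization protects the comparison from systematic bias with or without this covariate.

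What remains is that the article is not silent. It describes baseline variables with a one-year look-back for medication use only, and a model, and it points to neither the outcome's own baseline count nor a main analysis. The remedy is a specific covariate, two-thirds of which the trial's own system already displays.

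**Conclusion.** The point holds as a modest efficiency improvement on a secondary outcome. It is not an error that biases the utilization comparison, and it does not touch the primary outcome.

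Under the assumed inputs, adding the matching prior-year count reduces the variance of the treatment effect by 9% to 36% relative to the comparison with no stated covariates (r from 0.3 to 0.6). Relative to a model that already holds another useful baseline covariate, the reduction is about 1% to 5% for rare counts and 9% to 29% for frequent ones. The true position depends on the actual counts, their year-to-year correlation and which baseline factors are used, none of which the protocol states. The case for acting rests mainly on the low cost, and on fixing the covariate before outcome data are seen.

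**What to change.** - **Explanatory variables:** add the numbers of emergency department visits and hospitalizations in the 12 months before the index prescription. Add prior-year physician visits if the RAMQ extract used for the outcome can be drawn for that earlier year.
- **Data management and analysis:** state that the main analysis of each utilization component is the Poisson model (negative binomial if over-dispersed) with treatment group and the matching prior-year count as a prespecified covariate, for example log(count + 0.5). Keep the unadjusted rates as description.

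The cost is about one sentence in each of two sections, with no new patients, visits or staff. Physician visits may need a 12-month look-back in a data pull that is already planned. The rate ratio becomes conditional on prior use, which under a log link should lie close to the marginal one.

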### Blinding

Due to the nature of the study, blinding of patients and health-care providers will not be possible. However, we will blind personnel performing the interviews and physicians performing the assessment of ADE status of study group allocation.

### Sample size

We have based our sample size on the following assumptions:A baseline probability of non-persistence of 25% (based on a prior research study evaluating persistence with anti-hypertensive therapy using the same methods we will for this study) [11]A minimally clinical important difference of 20%A 10% loss to follow-up (based on our pilot study)An enrollment rate of 50% (based on our pilot study)Other specifications: α = 0.05, β = 0.20 and two-sided tests for significance will be used

Given these assumptions, we will need to approach 4,708 patients in total (2,354 patients in each treatment arm being eligible and approached for enrollment). This will result in 2,354 patients being enrolled (1,177 patients in each arm) and 2,118 patients evaluated for the composite outcome (1,059 patients in each arm). To be more conservative, we will enroll 1,100 patients in each arm.

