### Outcome assessment

#### Primary outcome: medication persistence at 180 days

We define persistence as ‘having a continuous supply of at least one medication used to treat the index condition, with gaps no greater than 90 days, in the first 6 months of treatment’. We will use validated methods to measure medication persistence using administrative claims data on prescription refills
[7–11]. Prescription refills provide a good proxy measure of medication use because refill rates are strongly correlated with targeted clinical outcomes such as blood pressure
[7]. We will construct medication dispensing histories for all patients and medications during the study follow-up period using the RAMQ medication file.

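### The enrolment target called more conservative is 77 per arm below the requirement just derived, and with the plan's own 10% loss gives about 76% power, not 80%

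*Protocol article*

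**What the plan says.** The Sample size section of the protocol article lists these assumptions:

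- "A baseline probability of non-persistence of 25"%
- "A minimally clinical important difference of 20"%, without saying whether this is relative or absolute
- "A 10% loss to follow-up (based on our pilot study")
- "An enrollment rate of 50% (based on our pilot study")
- "α = 0.05, β = 0.20 and two-sided tests for significance will be used"

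From these it derives 4,708 patients approached, 2,354 enrolled (1,177 per arm) and "2,118 patients evaluated for the composite outcome (1,059 patients in each arm"). The next sentence reads "To be more conservative, we will enroll 1,100 patients in each arm". The Abstract (Methods/design) confirms the operative number: 2,200 patients will be randomised.

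Data management and analysis specifies a simple chi-square test for the primary outcome. The section on the primary outcome, medication persistence at 180 days, says "We will construct medication dispensing histories for all patients and medications during the study follow-up period using the RAMQ medication file".

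**The concern.** Both 1,177 and 1,100 are enrolment figures. Moving from the larger to the smaller is the opposite of conservative, and no reason is given. The stated enrolment, loss and beta then cannot all be true together.

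At stake is how the result will be read. A null finding from this 2,200-patient trial would be judged against 80% power that its own assumptions do not deliver. Two further weaknesses in the section make this harder to see. The target effect has to be worked out backwards from the sample size. The calculation also names a composite outcome, whereas Primary objective and the primary outcome section define persistence alone.

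**Working it through.** **Inputs.** Control non-persistence p1 = 0.25, loss 10%, enrolment rate 50%, two-sided alpha 0.05 and beta 0.20 come from Sample size. The chi-square test comes from Data management and analysis. Taking the 20% difference as relative, p2 = 0.25 × 0.80 = 0.20 and d = 0.05. This is an assumption, tested in step 2.

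**1. The plan's own chain.** 1,177 × 0.9 = 1,059.3, and 2,354 / 0.5 = 4,708. The steps from approached to enrolled to evaluable are internally exact.

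**2. Which 20%?** Use the pooled two-proportion formula

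n = [1.960 × √(2 × p̄ × (1 − p̄)) + 0.842 × √(p1(1 − p1) + p2(1 − p2))]² / d².

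- Relative, 25% to 20%: p̄ = 0.225, so the square roots are √0.34875 = 0.5906 and √0.3475 = 0.5895. Then n = (1.1575 + 0.4961)² / 0.0025 ≈ 1,094 per arm.
- Absolute, 25% to 5%: n ≈ 49 per arm.

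Only the relative reading comes near the protocol's figures.

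**3. How close is 1,059?** It is about 3% below 1,094. Other common formulas give 1,091 (unpooled), 1,092 (arcsine) and 1,134 (continuity-corrected). The protocol names no formula, so this gap is minor. One observation: setting both variances at 25% gives 2 × 0.25 × 0.75 × (1.960 + 0.842)² / 0.0025 ≈ 1,177. This suggests, without proving, that 1,177 was the requirement before loss and that the loss was then deducted when it should have been added.

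**4. Effect of enrolling 1,100.** 1,177 − 1,100 = 77 fewer per arm (154 in total, 6.5%). With the stated loss, 1,100 × 0.9 = 990 evaluable per arm.

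**5. Power.** Power = Φ[(d√n − 1.1575) / 0.5895]. At n = 990: (0.05 × 31.464 − 1.1575) / 0.5895 = 0.705, and Φ(0.705) = 0.760.

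| Evaluable per arm | Arises from | Power |
|---|---|---|
| 990 | 1,100 enrolled, 10% loss | 76.0% |
| 1,045 | 1,100 enrolled, 5% loss | 78.2% |
| 1,059 | the plan's derived figure | 78.7% |
| 1,078 | 1,100 enrolled, 2% loss | 79.4% |
| 1,094 | 1,100 enrolled, about 0.5% loss | 80.0% |
| 1,100 | 1,100 enrolled, no loss | 80.2% |

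**6. Sensitivity to the formula.** At 990 per arm, the alternatives give 76.1% (unpooled), 74.3% (continuity-corrected) and 72.9% (both variances at 25%). All lie below 80% by more than 2 points.

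**7. What the shortfall means.** Of the 4.0 points lost, 80.0 − 78.7 = 1.3 are already in the 1,059, and 78.7 − 76.0 = 2.7 come from the cut to 1,100. With 990 per arm, the difference detectable at 80% power is 5.24 points (25% to about 19.8%, a 21% relative reduction). Enrolling 1,100 reaches the plan's 1,059 only if loss is at most 1 − 1,059/1,100 = 3.7%.

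**The case against.** **1,100 exceeds 1,059, so it may mean evaluable patients.** That would give 80.2% power. The text does not support it: the sentence speaks of enrolling, the Abstract speaks of randomising 2,200, and no larger enrolment that would leave 1,100 evaluable appears anywhere.

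**The 10% loss may not apply to the primary outcome.** This is the strongest objection. Persistence comes from RAMQ claims, for which dispensing histories are to be built for all patients, so a missed interview does not by itself remove the outcome. If loss is close to nil, the power shortfall largely disappears and the mislabelled sentence remains. This stands as a possibility, but 10% is the loss the section states. A reader might infer that 1,100 per arm simply gives 80%; the documents do not support that without a condition. Ethical considerations allows withdrawal, Administrative database interrogation requires record linkage, and the margin is only 6 patients per arm (1,100 − 1,094). Nor do the documents show that the loss was misapplied. The section sizes the trial for a composite outcome that is nowhere defined, and an interview-based component could have justified interview loss.

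**A reader might also infer that patients with complete claims will be dropped as lost.** The documents do not support this. Sample size only projects a number evaluated; no analysis set excludes patients who were not reached, and the primary outcome section refers to all patients.

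**The unlabelled 20% and the gap between 1,059 and 1,094 are small matters.** Agreed. The first is a point of clarity, since only one reading fits. The second is worth 1.3 points of power.

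**Conclusion.** The point holds. The sentence calling 1,100 per arm more conservative is wrong in direction: it is 77 per arm below the enrolment requirement derived immediately before it. Under the section's own 10% loss, the trial has 990 evaluable per arm and about 76% power (beta 0.24), so the stated beta of 0.20 is not met.

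The 76% rests on the relative reading of the 20% difference, the pooled chi-square formula, and the 10% loss applying to the primary outcome. Relaxing the loss assumption puts the deficit between 0 and about 4 points. The contradiction between the two enrolment figures needs none of these assumptions.

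**What to change.** In Sample size:

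1. Delete the claim that 1,100 per arm is more conservative.
2. Label the target as a 20% relative reduction in non-persistence, 25% to 20% (5 percentage points).
3. Choose one of two routes.
   - **Keep the 10% loss for the primary outcome.** Restate 2,200 enrolled (1,100 per arm), 990 evaluable per arm, about 76% power, and 2,200 / 0.5 = 4,400 approached.
   - **Justify a lower loss.** If the sponsor can show that claims-based persistence will be available for essentially all 2,200 randomised patients, say so, state the loss assumed and its power (80% only at about 0.5% loss or less; 79.4% at 2%; 78.2% at 5%), and apply the 10% loss to the 21-day interview outcomes.
4. Either way, replace the reference to a composite outcome with the persistence outcome as defined in the primary outcome section.

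The cost is wording in this section and, on the first route, a less favourable stated power. No extra patients are needed. If the sponsor prefers to keep both 80% power and 10% loss, enrolment would have to rise to 1,094 / 0.9 ≈ 1,216 per arm, which is 116 more per arm than planned.

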**Methods/design:**

We will randomly assign 2,200 adult ambulatory patients in the province of Québec who have been prescribed an incident medication for the management or prevention of a chronic health condition, to routine care or the ISTOP-ADE system. The ISTOP-ADE system consists of an interactive voice response system (IVRS) paired with pharmacist support. The IVRS will call patients at 3 and 17 days post-prescription to determine if they are experiencing any problems and connect them with a pharmacist when required or desired by the patient. We will evaluate medication persistence at 180 days and health-care utilization using provincial administrative data. Two blinded physicians will ascertain ADE status through a case review.

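### The enrolment target of 1,100 per arm is presented as the cautious choice, but it is 77 per arm below the plan's own calculation and gives about 76% power, not 80%

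*Protocol article*

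**What the plan says.** The Sample size section assumes 25% non-persistence under routine care, a minimally important difference of 20%, and "A 10% loss to follow-up (based on our pilot study"). It assumes that half of those approached will enrol. The error rates are fixed as "α = 0.05, β = 0.20 and two-sided tests for significance will be used". Whether the 20% is a relative or an absolute difference is not said.

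From these inputs the section reaches 4,708 patients to be approached, then "2,354 patients being enrolled (1,177 patients in each arm) and 2,118 patients evaluated for the composite outcome (1,059 patients in each arm"). The next sentence sets the target: "To be more conservative, we will enroll 1,100 patients in each arm". The abstract (Methods/design) confirms the lower figure as the one in force: "We will randomly assign 2,200 adult ambulatory patients in the province of Québec".

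The Data management and analysis section names a simple chi-square test for the primary outcome.

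**The concern.** A conservative adjustment to a sample size raises it. This one lowers it by 77 per arm, 154 in total, and gives neither a reason nor a revised power. The figure of 2,200 is the headline sample size. A reader will take it as giving at least 80% power with something in reserve, when the plan's own assumptions give less. That matters most if the primary comparison shows no significant difference, because the trial would be credited with more sensitivity than it was planned to have.

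**Working it through.** **Inputs.** Sample size section: control risk 0.25; difference 20%; two-sided alpha 0.05; beta 0.20; loss 10%; enrolment rate 50%; 1,177 calculated and 1,100 targeted per arm. Data management and analysis section: chi-square test. Normal quantiles: 1.960 and 0.842.

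**Reading the 20%.** As an absolute difference (25% to 5%), about 49 per arm would be enough. Only a relative reduction (25% to 20%, a difference of 0.05) comes near the plan's numbers, so that reading is assumed below.

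**The plan's own chain.**
- 4,708 × 0.5 = 2,354 enrolled; 2,354 / 2 = 1,177 per arm.
- 1,177 × 0.9 = 1,059.3, which matches the 1,059 evaluated per arm.

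These steps agree with one another. The section names no formula for the starting figure, but one common simplification, with the control-arm variance used in both arms, returns it:

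2 × (1.960 + 0.842)² × 0.25 × 0.75 / 0.05² = 1,177.3

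A formula of this kind gives the number to be analysed. If it was the one used, the 10% loss was deducted from the required number when enrolment should have been inflated to cover it. This is an inference from the numerical match.

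**Number required by the usual formula (pooled variance under the null).**

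n = [1.960 × √(2 × 0.225 × 0.775) + 0.842 × √(0.25 × 0.75 + 0.20 × 0.80)]² / 0.05² = 1,094 analysed per arm

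The unpooled version gives 1,091, the arcsine version 1,092, and the continuity-corrected version 1,134. With 10% loss, 1,094 / 0.9 = 1,216 enrolled per arm.

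**What the target delivers.** 1,100 × 0.9 = 990 analysed per arm. Power is

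Φ{[0.05 × √n − 1.960 × √(2 × 0.225 × 0.775)] / √(0.25 × 0.75 + 0.20 × 0.80)}

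At n = 990: Φ[(1.573 − 1.157) / 0.589] = Φ(0.705) = 0.760.

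| Analysed per arm | Origin | Power, usual formula | Power, control variance in both arms (inferred) |
|---|---|---|---|
| 990 | 1,100 less 10% | 76.0% | 72.9% |
| 1,059 | 1,177 less 10% | 78.7% | 75.7% |
| 1,100 | target, no loss | 80.2% | 77.3% |
| 1,177 | calculated, no loss | 82.8% | 80.0% |

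At 990 the arcsine approximation gives 76.0% and the unpooled 76.1%. A simulation of the chi-square test (400,000 trials) gives 76.0%. With continuity correction it is 74.3%.

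**Number to approach.** At 50% enrolment, 2,200 enrolled needs 2,200 / 0.5 = 4,400 approached. The printed 4,708 belongs to the 2,354 that the target replaced.

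**The case against.** Four points can be made for the plan.

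- **The reversed loss step is inferred.** The section labels 1,177 as enrolled and 1,059 as evaluated, and 1,059 / 0.9 = 1,176.7, so the printed figures also fit a correct inflation from 1,059. This stands. The powers in the last column of the table, and any type II error above about 24% drawn from them, depend on the inferred formula. The main result does not: the usual formula gives 78.7% at 1,059 and 76.0% at 990.
- **Loss may be smaller than 10%.** Persistence is measured from provincial dispensing claims, and every participant must use that insurer. Power would be 78.2% with 5% loss, 79.4% with 2% and 80.2% with none. But the Sample size section itself applies the 10% to the number evaluated, and even with no loss there is no margin that could be called conservative.
- **1,100 may have been meant as the analysed number**, for instance 1,094 rounded up. The text says these patients will be enrolled, and the abstract says 2,200 will be randomised. If 1,100 were to be analysed, about 1,222 per arm (1,100 / 0.9) would have to be enrolled.
- **The effect is modest.** The shortfall is four points of power. It leaves the type I error and the test untouched, and the confidence interval will show how precise a null result is. This bears on how serious the error is. The sentence remains wrong.

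**Conclusion.** The concern holds. The target is 77 per arm below the plan's calculated enrolment, so the claim of conservatism is wrong. On the stated assumptions, 990 per arm are analysed and power is about 76%, against a stated 80%. That is 104 per arm (about 10%) short of the 1,094 that the usual formula requires. Of the four points lost, about 2.7 come from the cut to 1,100 (78.7% to 76.0%). The other 1.3 were already missing at the plan's 1,059.

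The result rests on the 20% being a relative reduction, on the 10% loss applying to the primary outcome as the section applies it, and on a chi-square test without continuity correction.

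**What to change.** Remove the claim that 1,100 is conservative and choose one of two routes.

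1. **Keep 1,100 per arm.** State that this is below the 1,177 calculated; that 4,400 patients will be approached at 50% enrolment; that 990 per arm will be analysed after 10% loss; and that power is about 76% for a fall from 25% to 20% with a two-sided 0.05 chi-square test. If the sponsor expects near-complete claims data, add that 80% power needs about 1,094 of the 1,100 per arm to have the outcome. This changes wording only, and the stated power becomes slightly less favourable.
2. **Keep 80% power with 10% loss.** Show the loss as an inflation: 1,094 / 0.9 = 1,216 enrolled per arm, 2,432 in total, with 4,864 approached. If the sponsor confirms that 1,177 was the number to be analysed, the figure is 1,177 / 0.9 = 1,308 per arm. This costs 232 or 416 more patients than the current 2,200.

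Under either route, name the formula used, so that required number and power come from the same one, and state that the 20% is relative (25% to 20%). Carry the final total into the abstract.
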